#### Student randomization

Upon determination of eligibility, students will be randomized in a 2:1 ratio to TMCU or waitlist/control. This will occur after blocking by student gender and grade-level, independently at each school. The trial seeks 250 student participants during its 24-month period of TMCU implementation.

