### Hypothesis testing and analytic approach

Hypotheses focus on comparative utility of two technical assistance methods on implementation outcomes among TMCU interventionists and intervention effectiveness among students. Hypothesized effects are that the (1) longitudinal effects of interventionists receiving ‘gold-standard’ vs. ‘as-needed’ technical assistance will not differ, with the latter method proving more cost-beneficial and cost-effective; and (2) effects of technical assistance method for intervention impact on student marijuana use frequency will not differ, with greater reduction expected of students randomly assigned to TMCU vs. waitlist/control.

Trial analyses will be governed by an investigative team member (KK), experienced as a biostatistician and methodologist in adolescent health research. Given nesting of trial data (i.e., repeated observations of students, nested in interventionist caseloads; interventionists nested in schools), multilevel models will include progressive taxonomies in model-building. Initially, an unconditional model will estimate variance of random effects, and a subsequent unconditional growth model will identify the appropriate shape of and variability in rate of change over time for hypotheses involving repeated measures. Technical assistance condition will then be included in conditional models with predictors, with relevant covariates added to determine robustness of main effects and relative goodness-of-fit for each successive model via likelihood ratio tests and deviance statistics. Power analyses (.80, *p* < .05) inform proposed recruitment of (1) 30 interventionists to detect longitudinal effects of training and technical assistance consistent with those for other lay counselors (Cohen’s *d* = 1.00); and (2) 250 students to detect small intervention effects (Cohen’s *d* = .35) relative to waitlist/control.

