#### Hypothesis 1a: comparable utility of technical assistance methods

A non-inferiority paradigm, traditionally used to show a novel treatment is not statistically different than an established one, will test study hypotheses. This paradigm will be applied to interventionists’ longitudinal implementation outcomes, principally TMCU fidelity (i.e., R:Q, %OQ, %CR) in SP interactions but also secondary outcomes of TMCU knowledge, attitudes, adoption readiness, and satisfaction. Initial effects are consistent with training intent, with analyses testing if ‘gold-standard’ and ‘as-needed’ technical assistance produce equivalent longitudinal impacts. If (as expected) the number of schools recruited is small, they will be dummy-coded and treated as fixed effects. Point-estimates and confidence intervals from the model will be included in non-inferiority tests, examining each technical assistance method for (1) pre-post change in implementation outcomes, (2) mean implementation level by TMCU interventionists over time, and (3) differential rate of change in implementation over time. As recommended [75], a ½ standard deviation (SD) difference will serve as the a priori non-inferiority margin. If the lower bound of two-sided 95% confidence interval of between-method differences exceeds this margin, a test of superiority will specify the direction and magnitude of differential impact of the technical assistance methods.

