#### Hypothesis 1b: comparable clinical effectiveness of technical assistance methods

For student outcomes, multilevel models extend to three levels for repeated observation of marijuana use frequency and secondary outcomes (i.e., problems, motives, perceptions, self-efficacy to abstain, academic performance, and engagement) nested within interventionists. A primary test parameter is the interaction of time × technical assistance method of the TMCU interventionist as a dummy-coded predictor. As temporal effects may not conform to simple linear growth curves, models will test different specifications of time (i.e., piecewise, polynomial, or other nonlinear approaches). The a priori non-inferiority margin (i.e., ½ SD) will again be applied and, if exceeded, a test of superiority will specify the direction and magnitude of differential impact.

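### The ½ SD student margin exceeds the d = .35 TMCU effect the trial is powered to detect, so meeting it does not by itself show that any TMCU benefit is kept

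*Protocol article*

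**What the plan says.** The margin first appears in the protocol article under Hypothesis 1a, for interventionist fidelity and related staff outcomes: "As recommended [75], a ½ standard deviation (SD) difference will serve as the a priori non-inferiority margin". The decision there rests on a two-sided 95% confidence interval for the difference between methods.

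Hypothesis 1b then turns to student outcomes, marijuana use frequency first, and carries the same margin over: "The a priori non-inferiority margin (i.e., ½ SD) will again be applied". It gives no separate reason for using ½ SD on a student outcome.

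The section on hypothesis testing and analytic approach sizes the student sample differently, with "250 students to detect small intervention effects (Cohen’s *d* = .35) relative to waitlist/control". No other student effect size is stated. The same section pairs the comparability hypothesis with an expected greater reduction in use under TMCU than under waitlist, for all TMCU students together. It does not require TMCU students of as-needed interventionists, taken alone, to do better than waitlist students.

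**The concern.** A non-inferiority margin is meant to rule out an unacceptable loss of the comparator's benefit. Here the comparator is TMCU delivered under gold-standard assistance. The only benefit quantified for TMCU is .35 SD, and the margin is .50 SD. If gold-standard TMCU is worth .35 SD and as-needed TMCU is worth nothing, the true difference between methods is .35 SD, which is inside the margin. A result that meets the rule would therefore be compatible with no benefit at all under as-needed assistance.

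Comparing the two methods on intervention effectiveness is one of the co-primary aims. The Conclusions look ahead to using the fidelity alarm with other therapies and in other settings, so the wording of a positive result matters.

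**Working it through.** **Inputs from the article.** Student margin .50 SD. Planning effect d = .35 for TMCU vs waitlist, power .80, p < .05. 250 students, 2:1 to TMCU or waitlist, so about 167 and 83. 30 interventionists. Two-sided 95% interval.

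**Assumptions of mine.** Both SD figures share one scale. TMCU students split equally between methods (83.5 each, 15 interventionists each). Interventionist ICC 0 to .10. No dropout.

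**1. The plan's own figure.** For d = .35 and SD 1, two-sided .05:
- 1:1 allocation: 258 students for 80% power; power with 250 is .79.
- 2:1 allocation: 291 students; power with 250 is .74.
- 2:1, one-sided .05: 228 students, and 228/.90 = 254 after 10% dropout.
- 2:1, two-sided, adjusted for a baseline with assumed correlation .4: 243 students.

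The stated 250 is thus recovered under ordinary variants, and d = .35 can be taken as the planning value.

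**2. Margin against effect.** .50/.35 = 1.43. With gold-standard TMCU at .35, the edge of the margin puts as-needed TMCU at .35 − .50 = −.15 SD relative to waitlist.

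**3. Standard error of the between-method difference.** Students per interventionist m = 83.5/15 = 5.57. Design effect DE = 1 + (m − 1) × ICC, which is 1.00 at ICC 0 and 1.457 at ICC .10. SE = √(2 × DE/83.5) = .155 and .187. With 28 df the critical value is 2.048. Non-inferiority is declared when the estimated loss is below .50 − 2.048 × SE, that is .183 (ICC 0) or .117 (ICC .10).

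**4. Chance of declaring non-inferiority (noncentral t, 28 df).**

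| True loss under as-needed | ICC 0 | ICC .10 |
|---|---|---|
| 0 | 88% | 73% |
| .175 SD (half of .35) | 53% | 39% |
| .35 SD (all) | 15% | 12% |

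Had the margin been .35, the last row would be 2.5%. A normal approximation gives 16% to 12% for that row.

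**5. Adding the pooled TMCU vs waitlist test, under total loss.** Gold-standard at .35 and as-needed at 0 give a pooled effect of .175.
- ICC 0: SE = √(1/167 + 1/83) = .134, and the pooled test succeeds about 26% of the time.
- ICC .10, design effect on TMCU students only: about 23%.
- ICC .10, design effect on waitlist students too: SE = √(1.457 × (1/167 + 1/83)) = .162, about 19%.

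With equal arms the sum and the difference of the two method means are uncorrelated, so the probabilities multiply: .153 × .256 = .039 at ICC 0; .118 × .228 = .027, or .118 × .19 = .022, at ICC .10. Both succeed about 4% to 2% of the time.

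**6. Power at smaller margins, true difference 0.** Margin .35: 59% (ICC 0) to 44% (ICC .10). Margin .175: 19% to 15%.

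**7. As-needed TMCU vs waitlist at d = .35.** SE = √(DE/83.5 + 1/83) = .155 to .172, giving power of about 62% to 53% (normal approximation).

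**The case against.** The best reply is that .35 is an effect the sample can detect, not a forecast of what TMCU will do, and that it pools TMCU students under both assistance methods. That stands. If the pooled effect were exactly .35 and as-needed contributed nothing, gold-standard would have to be .70. The difference would then lie outside the margin, and non-inferiority would almost never be declared. On that pooled reading with equal arms, the edge of the margin is gold-standard at .35 + .25 = .60 and as-needed at .35 − .25 = .10. As-needed would still be above waitlist, although .50/.60 = 83% of the gold-standard effect would be gone. The total-loss scenario therefore assumes gold-standard TMCU at .35, and so a pooled effect of .175.

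It is also fair that the article cites a source for ½ SD, which cannot be checked here, and that it does not define the SD. Neither point supplies a reason for a student margin above the only student effect stated.

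A reader might infer three stronger things that the article does not support:
- **That a false claim of comparability is likely.** Under total loss it occurs 12% to 15% of the time, and about 2% to 4% of the time if the pooled TMCU test must also succeed.
- **That the margin can drift with the coding of time.** The article does say "As temporal effects may not conform to simple linear growth curves, models will test different specifications of time", but it also has an unconditional growth model identify the shape of change before assistance condition enters. It nowhere states the margin per visit or per unit of slope. The exact contrast is commonly left to a full protocol or SAP.
- **That the margin ought to be half the effect, .175.** Nothing in the article fixes that fraction.

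**Conclusion.** The point holds in a limited form. The student margin is larger than the only TMCU effect in the article, by a factor of 1.43. No rule requires as-needed TMCU alone to beat waitlist before comparability is claimed. Meeting the ½ SD rule therefore does not, on its own, show that students under as-needed assistance keep any benefit.

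The practical weakness is greatest for partial loss: half of the planning effect could go and the rule would still be met in roughly four to five trials out of ten. The size of the problem rests on a shared SD scale, gold-standard TMCU at .35, equal numbers per method and the assumed ICC range. A larger true effect would soften it: at .50 the margin equals the effect, and at .80 it is about 62% of it. The article states no such effect.

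**What to change.** In Hypothesis 1b:

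1. State that a result within ½ SD does not by itself support comparable clinical effectiveness.
2. From the same model, report as-needed TMCU vs waitlist and gold-standard TMCU vs waitlist, each with a 95% confidence interval. Claim comparability only if as-needed TMCU also beats waitlist.
3. Report the between-method difference as an estimate with its 95% confidence interval.
4. Either justify the student margin against the .35 planning effect, or set it below .35 and restate the power. For orientation, power is about 44% to 59% at a margin of .35 and 15% to 19% at .175, for ICC .10 to 0.

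The cost is wording and two contrasts from data already planned. The article reports that school recruitment has begun and interventionist enrolment is still to come, so on that status the change would precede student data. The real price is that a formal claim of comparability becomes less likely: the as-needed vs waitlist contrast has only about 53% to 62% power even if as-needed TMCU keeps the full .35.

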### Trial regulation and current status

In accordance with National Institute on Health policy, a Data Safety and Monitoring Board (DSMB) was assembled to whom the principal investigators (BH, DW) recurrently report trial progress. Content expertise of this three-member, university-based DSMB encompasses school-based health service implementation, brief interventions, and community-participatory addiction research. The trial coordinator (LM) received approval for all procedures from the University of Washington Institutional Review Board to whom protocol modifications and adverse events will be reported, obtained a Certificate of Confidentiality, and registered the trial at ClinicalTrials.gov (NCT03111667). As for trial progress, recruitment of local schools has been initiated with formal enrollment of TMCU interventionists expected in the months to come.

## Discussion

As schools are a common point-of-contact for students in the USA to access behavioral health services [21, 22], there are several reasons this has potential to address marijuana use. First, most adolescents who misuse substances evidence marijuana use disorder [7], a leading impetus for youth treatment admissions [8]. Second, progressive legislation of medical/recreational marijuana use widens its public availability and cultural permissibility [13], while risk perceptions among high school students continually decline [12]. Third, over 95% of teens with a substance use disorder continue to attend school—so school-based services should offer significant reach [76]. Taken together, these issues underscore need for effective, affordable strategies to support transport of efficacious, marijuana-focused health services for use by school-based personnel. The described trial—and its testing of a fidelity alarm bell as a method of purveyor technical assistance—is designed to offer one such effort. Resulting trial findings are likely to hold implications for similar service transportability challenges across a range of health services and the community-based settings for which they are appropriate.

### Innovation and potential impact

The described trial offers innovation at multiple levels. Most broadly, its findings will address a salient gap in implementation science literature through examination of processes for purveyor introduction and support of an empirically supported health service. Though this trial will specifically examine implementation of a brief marijuana-focused intervention in schools, replication of many design features described herein may be appropriate for other trials. At the level of implementation strategies, this trial will test a novel approach whereby technical assistance is provided to school-based staff after initial training. As technical assistance processes remains an understudied topic [77], a clinically useful, affordable means to provide such support may hold considerable impact for therapy purveyors and community settings. Notably, the ‘fidelity alarm bell’ to be tested retains core elements (i.e., purveyor fidelity monitoring, feedback, coaching) recommended for implementing MI/MET [41] and other therapies [39, 40]. A final point concerns potential future interplay with ongoing validation work on automated MI/MET fidelity assessment methods that code session recordings via computer and transform fidelity indices as visual feedback [78]. If feasible, future work may pair a fidelity alarm bell with these promising natural language processing approaches to streamline fidelity-monitoring processes [79–81] and thereby boost the efficiency and scale with which they occur. Diminished purveyor burden in this area may open possibilities to enhance feedback/coaching processes [82], or simply reduce purveyor reliance in favor of localized, self-sustaining quality assurance methods [48].

### Limitations

Design caveats bear mention. Potential for selection bias exists for participating schools, interventionists, and students. Recruitment of schools that collaborated on prior TMCU trials may undermine generalizability of results, though both the multisite design and broad inclusion criteria for settings and interventionists mitigate this concern. With respect to TMCU effectiveness, student inclusion/exclusion criteria are consistent with those of prior efficacy trials and the intent of this targeted intervention [27]. The trial responds to local demands in Washington state, where legalization of recreational marijuana use among adults has amplified public concern and demand for preventative services. Persisting variation in legislative marijuana policy, both domestically and abroad [83], suggests this local context be considered in eventual interpretation of trial findings. Measurement choices present additional caveats. Trial aims necessitate audio-recording of TMCU sessions, which for some may introduce social anxiety and impression management. These concerns appear not to extend to planned SP interactions, given strong evidence for valid, reliable MI fidelity estimates via this methodology [84]. Reliance on student-report instruments to examine TMCU effectiveness is another caveat, particularly for marijuana use—though use of invasive biological testing with minors would introduce greater scientific and pragmatic concerns. As in any trial, potential influence of unassessed third variables is a possible limitation. Further, alternative trial designs (i.e., cluster-randomization, stepped-wedge) may offer some potential benefits in efficiency, albeit not without introducing other unwanted caveats.

## Conclusions

This trial offers potential advancement for the implementation science field, specifically in its thorough examination of a data-driven technical assistance method to support long-term implementation of a marijuana-focused MET intervention in schools. If shown to be clinically useful and affordable, the concept of a fidelity drift alarm could be readily translated—alone or in future conjunction with emerging methods to automate MI/MET fidelity-monitoring—for use with other empirically supported therapies and in other settings. The described trial adds to other recent efforts [85] in furthering momentum for the adoption and effective implementation of efficacious therapies for youth populations through a focus on methods of purveyor technical assistance to assure quality in therapy delivery.

## Abbreviations

%CR: Percentage of reflections deemed to be ‘complex’
%OQ: Percentage of questions deemed to be ‘open’
DSMB: Data Safety Monitoring Board
EPIS: Exploration, Preparation, Implementation, Sustainment
MET: Motivational enhancement therapy
MI: Motivational interviewing
MINT: Motivational Interviewing Network of Trainers
R:Q: Ratio of reflections to questions
SD: Standard deviation
SP: Standardized patient
TMCU: Teen Marijuana Check-Up
